### Study Objectives and Hypothesis

We designed the HELI study (derived from the Dutch “HErsenfuncties na LeefstijlInterventie,” meaning “Brain function after lifestyle intervention”) to better understand the neurocognitive effects of a multidomain lifestyle intervention and underlying peripheral (central) mechanisms. The HELI study is a 6-month multidomain lifestyle intervention in older adults at risk of cognitive decline (based on lifestyle-modifiable cardiovascular risk factors) with a high and low-intensity intervention arm. We focus on 5 different lifestyle domains within the intervention period: diet, physical activity, stress management and mindfulness, cognitive training, and sleep. We will assess effects on multiple neuroimaging brain measures (primary: working memory task-related fMRI responses and performance, and quantitative imaging of CBF), peripheral measures related to the gut-immune-brain axis (primary: blood inflammatory profile and fecal microbiota composition), as well as their connections. We propose that, compared to the low-intensity group, the high-intensity group will show greater improvement in central neuroimaging outcomes (eg, fMRI and CBF) as well as peripheral outcomes (eg, blood inflammatory profile and fecal microbiota composition). Moreover, we hypothesize that individual changes in central outcomes correlate with changes in peripheral outcomes, as summarized in Figure 1.

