### Primary Outcomes

The primary outcomes are the changes between baseline (T0) and follow-up after 6 months (T1) in:

Brain activity during working memory in dlPFC [124] and hippocampus (Harvard-Oxford atlas), using fMRI blood-oxygen-level-dependent (BOLD) activity and task accuracy during a numerical N-back task [125];Cerebral perfusion levels, measured by MRI arterial spin labeling in dlPFC and hippocampus;Peripheral immunometabolic biomarker levels in blood plasma (inflammation markers IL-6, TNF-α, hs-CRP) and feces microbiota diversity (Shannon- and phylogenetic diversity) and richness (Chao1).

In addition, we will investigate intervention-induced gut-immune-brain links by assessing the relation between the effects found in the abovementioned primary peripheral markers and brain outcome measures.

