### Sample Size

The expected effect size for this study was determined based on other, mostly single-domain, lifestyle intervention studies with similar outcomes as our primary outcomes in the brain (eg, cerebral perfusion, working memory assessments) and in the periphery (eg, immunometabolic biomarkers, gut microbiome diversity). These studies generally found medium-to-large effect sizes (see Table S4 in Multimedia Appendix 1 [52,53,95,106,107,153-161]). Therefore, we deemed a slightly above-medium effect size of 0.30 (Cohen f[V]) suitable for our primary outcomes from baseline (T0=week 0, before start intervention) to follow-up (T1=week 26, after end intervention). The sample size calculation was performed using G*Power (version 3.1.9.6; Universität Kiel [162]). Using a multivariate ANOVA (with repeated measures and within-between interaction) *F* test with a power of 80% and a 2-tailed α-error probability of .05, we calculated that a total of 90 study participants would be required. However, based on our experience with previous fMRI and intervention studies, we expect a potential loss of data of 15% due to poor fMRI data quality (eg, motion artifacts) and potential intervention drop-outs. Therefore, to reach sufficient power, we would require a total sample size of 104 (90 participants×15% potential data loss=103.5=104) participants in this study.

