### Methods: Statistics and Analysis

We will test for change between T0 and T1 in the primary and secondary outcome variables, both within-group and between-group, using linear mixed-effect models with random effects for intercept (individuals). The intervention group and time will be included as fixed effects, as well as the interaction term between intervention group and time, to model the difference in change between T0 and T1 as a function of group allocation.

In addition, we will test for correlations in change (T0 minus T1) between (primary) brain outcomes and (primary) peripheral outcomes. We will select an appropriate correlation test for our data, based on whether assumptions are met. We will include both the high- and low-intensity groups if there is enough variance in change across both groups; else, we will only include the high-intensity group.

The level of significance will be set at 0.05 (2-sided). FDR correction will be used to account for multiple comparisons of secondary and exploratory outcomes. FWE correction will be used for secondary whole-brain analyses.

As part of exploratory analyses to assess the domain-specific effects on our primary outcome measures, we will take the pre- and posteffects of the primary outcome measures and use domain-related questionnaire scores and smartwatch-derived physiological data as a measure of improvement for each respective domain as predictors in linear mixed-effect models.

We will perform an intention-to-treat analysis. Participants who withdrew from the study during the 6-month intervention period, but had not withdrawn consent, were invited to the T1 (after week 26) follow-up outcome assessments. This means that we will use all available collected data, including collected (follow-up) data of participants who dropped out of the intervention. Missing data or data with insufficient quality, however, will not be used in the analysis.

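### The brain-periphery change correlations use a population chosen from the data with no threshold and name no arm term, so pooled links could reflect arm effects alone

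*Protocol article*

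**What the plan says.** Under Methods: Statistics and Analysis, the article says "we will test for correlations in change (T0 minus T1) between (primary) brain outcomes and (primary) peripheral outcomes". The type of test is left open: "We will select an appropriate correlation test for our data, based on whether assumptions are met". Both arms enter "if there is enough variance in change across both groups; else, we will only include the high-intensity group". The article does not define the variance measure, set a cut-off, or say whether the choice is made once or for each pair of outcomes.

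The same section names arm for the mixed models ("The intervention group and time will be included as fixed effects, as well as the interaction term between intervention group and time") but not for the correlations.

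Study Objectives and Hypothesis states the target: "we hypothesize that individual changes in central outcomes correlate with changes in peripheral outcomes". It also predicts that "the high-intensity group will show greater improvement in central neuroimaging outcomes (eg, fMRI and CBF) as well as peripheral outcomes". Primary Outcomes describes the same work in other terms: "we will investigate intervention-induced gut-immune-brain links by assessing the relation between the effects found".

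**The concern.** The question in Study Objectives is whether people whose peripheral markers change more also show more change in the brain. If the intervention moves a brain outcome and a peripheral outcome separately, arm is a common cause of both changes. High-intensity participants then tend to sit at one end of both scales and low-intensity participants at the other. A correlation over the pooled sample picks this up even if the two changes are unrelated within each arm. When both outcomes improve, the artefact has the hypothesized sign.

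The population rule adds a second problem. The analyst decides after seeing the data whether about half the sample is used, against no stated criterion. If the rule refers to the pooled variance of change, an arm shift itself raises that variance. The rule would then lean towards pooling when pooling is most affected by arm.

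At stake is the trial's mechanistic reading. An intervention that acts on two systems independently could be reported as evidence that one is linked to the other within individuals.

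**Working it through.** **Inputs from the article.** Effect size: "we deemed a slightly above-medium effect size of 0.30 (Cohen f[V]) suitable for our primary outcomes" (Sample Size), with 80% power, two-sided 0.05 and 90 evaluable participants. Randomized: 53 high-intensity and 49 low-intensity, 102 in total (Results). Expected data loss: 15% (Sample Size).

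**Assumptions not in the article.** Change scores are normal with unit SD within arm. The within-arm correlation is zero, which is the null for an individual-level link. The arm shift on each change score is d, varied from 0 to 1.0. After 15% loss, 0.85 × 102 ≈ 86 participants remain, of whom 0.85 × 53 ≈ 45 are in the high-intensity arm.

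**Step 1: reproduce the plan's figure.** For two groups and two times, the interaction F test has 1 and N − 2 degrees of freedom and noncentrality f² × N. At f = 0.30, power is 0.799 at N = 89 and 0.804 at N = 90, so the stated 90 is recovered. The noncentrality is 0.09 × 90 = 8.1. A two-sample comparison of change with 45 per arm has d² × 45/2, which is also 8.1 at d = 0.6. The design effect is therefore a 0.6 SD difference in change.

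**Step 2: pooled correlation from arm effects alone.** With proportion p in one arm and shift d on both variables:

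r = p(1 − p)d² / (1 + p(1 − p)d²)

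- d = 0.3, p = 0.5: 0.0225/1.0225 = 0.022
- d = 0.6: 0.09/1.09 = 0.083
- d = 1.0: 0.25/1.25 = 0.20

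The denominator shows that the pooled variance of each change score rises by 9% at d = 0.6.

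**Step 3: false-positive rate per pair.** Check by Fisher z at n = 86 and d = 0.6: atanh(0.083) × √83 ≈ 0.75. The rejection probability is P(Z > 1.96 − 0.75) + P(Z < −1.96 − 0.75) ≈ 0.117. At d = 1.0 the same calculation gives 0.455. Simulated rates for a pooled Pearson test are:

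| Shift on the two outcomes (SD) | Pooled, unadjusted | Arm-adjusted |
|---|---|---|
| 0 and 0 | about 5% | about 5% |
| 0.6 and 0 | about 5% | not run |
| 0.3 and 0.3 | 5.4% (n = 90), 5.5% (n = 102) | about 5% |
| 0.6 and 0.3 | about 7% | not run |
| 0.6 and 0.6 | 12.0% (n = 90), 13.0% (n = 102) | 5.0%, 5.1% |
| 1.0 and 1.0 | 48% (n = 90), 54% (n = 102) | about 5% |

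**Step 4: cost of dropping an arm.** Detectable r at 80% power = tanh(2.80/√(n − 3)).

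- All randomized: tanh(2.80/√99) = 0.27 for 102; tanh(2.80/√50) = 0.38 for 53.
- After 15% loss: tanh(2.80/√83) = 0.30 for 86; tanh(2.80/√42) = 0.41 for 45.

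For a true within-arm r of 0.30 with everyone analysed, power is 0.87 with both arms and 0.60 with the high-intensity arm only.

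**Step 5: cost of adjusting for arm.** For a true r of 0.30 and n = 102, power is 0.870 adjusted and 0.873 unadjusted.

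**Step 6: the variance rule by itself.** One assumed version of the rule pools only if the low-arm variance is at least 90% of the high-arm variance on both outcomes. With 45 + 41 participants and no arm effect, the false-positive rate was about 5%.

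**Step 7: number of pairs.** Five brain measures (BOLD in two regions, task accuracy, CBF in two regions) by six peripheral measures (three inflammation markers, two diversity indices, one richness index) give 30 pairs.

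**The case against.** The strongest reply is that the article never says the pooled correlation is unadjusted. It promises a suitable test, which could be a partial correlation, and an analysis plan that is not shown may specify one. This stands: a reader might infer that the trial has decided against arm adjustment, but the text only fails to name it. The reply does not reach the population rule, which is written down and is open.

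It can also be said that Primary Outcomes speaks of links induced by the intervention, so a joint arm shift is part of what is sought. That stands as a second estimand. It is not the individual-level association in Study Objectives, and a pooled correlation mixes the two.

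Three stronger readings are tempting, and the documents do not support them.

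- A reader might multiply the 12% rate over all 30 pairs and expect about 3.5 false links. That needs a 0.6 SD shift on all 11 outcomes at once. The article adopts 0.30 as a planning value for its primary outcomes, which does not show that every one will shift that far.
- A reader might treat the choice of population as picking the better p-value, which would give about 8% with no arm effect. The stated rule turns on variance, and the version simulated in step 6 held the error at about 5%.
- A reader might say the links clearly escape multiplicity control because they appear under Primary Outcomes. They are introduced there as an addition to the listed outcomes, and FDR is assigned to secondary and exploratory outcomes. Coverage is ambiguous, not plainly absent.

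**Conclusion.** The point holds in a limited form and should be fixed. The population rule depends on the observed data and has no threshold. The pooled analysis as described, if run without an arm term, does not isolate the individual-level association that the article hypothesizes.

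The size depends on the arm effects. Inflation is negligible when only one outcome of a pair shifts or both shift by 0.3 SD, modest at the design effect on both, and large at 1.0 SD, which is well above the design effect. These figures assume normal change scores, equal SDs in the two arms and no within-arm association. The loss from using one arm is a matter of precision and does not depend on arm effects; the 86 and 45 figures rest on the assumed 15% loss falling equally on both arms. The variance rule was not shown to inflate error by itself when there is no arm effect. The between-arm mixed models already include group and its interaction with time and are unaffected.

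**What to change.** - Set both arms as the primary population for the change correlations, and remove the variance condition.
- Test each pair with an arm-adjusted partial or rank correlation, or regress brain change on peripheral change with arm as a covariate.
- Keep the high-intensity-only analysis as a sensitivity analysis.
- If the joint intervention-induced shift is also of interest, report the unadjusted pooled correlation separately and say that it is not evidence of an individual-level link.
- State that the FDR correction covers the 30 brain-by-peripheral pairs.

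The cost is analysis wording and one degree of freedom per test. No new data are needed.

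### By its stated scope, the multiplicity correction leaves out the eleven primary outcomes, so each group-by-time test runs at unadjusted 0.05

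*Protocol article*

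**What the plan says.** The Primary Outcomes section, matching the Abstract, names changes over six months in three groups of measures.

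- Task fMRI: "Brain activity during working memory in dlPFC" and in hippocampus, "using fMRI blood-oxygen-level-dependent (BOLD) activity and task accuracy during a numerical N-back task".
- Arterial spin labelling perfusion in the same two regions.
- Blood and stool markers: "Peripheral immunometabolic biomarker levels in blood plasma (inflammation markers IL-6, TNF-α, hs-CRP) and feces microbiota diversity (Shannon- and phylogenetic diversity) and richness (Chao1").

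Methods: Statistics and Analysis sets out the testing: "We will test for change between T0 and T1 in the primary and secondary outcome variables, both within-group and between-group". The between-group question is carried by the group-by-time term of a linear mixed model. On error control the same section makes three statements:

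- one two-sided level of 0.05 is fixed, without reference to any class of outcome;
- the false discovery rate is then addressed for two classes: "FDR correction will be used to account for multiple comparisons of secondary and exploratory outcomes";
- for imaging beyond the regions of interest, a different method is named: "FWE correction will be used for secondary whole-brain analyses".

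The Sample Size section calculates 90 participants for an effect size f(V) of 0.30, with "a power of 80% and a 2-tailed α-error probability of .05", and raises this to 104 for data loss.

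**The concern.** The article allocates multiplicity control class by class, and the primary class is in neither allocation. It names no lead outcome, testing order or composite, and no rule for how many primary outcomes must succeed. Followed as written, the plan corrects the secondary results and leaves the primary ones uncorrected, so the outcomes that carry the main conclusions have the weakest protection.

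What is at stake is how a mixed result would be read. Study Objectives and Hypothesis predicts greater improvement in the high-intensity group on central and peripheral outcomes. With eleven separate chances at 0.05, one nominally significant marker could be reported as a positive primary finding, and the plan gives no basis for discounting it.

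**Working it through.** **Count of primary variables (Primary Outcomes).** BOLD in two regions (2), n-back accuracy (1), perfusion in two regions (2), inflammation markers (3), microbiota indices (3): 2 + 1 + 2 + 3 + 3 = 11.

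**The plan's own figure first.** With two groups and two time points, the within-between interaction has 1 and N − 2 degrees of freedom and noncentrality λ = N × 0.30² = 0.09N. At alpha 0.05:

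- N = 89: power 79.9%
- N = 90: λ = 8.1, power 80.4%

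So 90 is the smallest N reaching 80%, and the stated figure reproduces. It reproduces for a single test of one outcome at unadjusted 0.05. The multivariate label in Sample Size therefore does not stand for a joint test over the eleven outcomes.

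**Chance of at least one significant primary outcome when none truly differs.** With independent tests:

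1 − 0.95¹¹ = 0.431, or 43%. The expected number of false positives is 11 × 0.05 = 0.55.

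The documents give no correlations between outcomes, so the values below are assumptions. They come from simulation of eleven two-sided tests under the global null. Families are BOLD (2), accuracy (1), perfusion (2), inflammation (3) and microbiota (3).

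| Assumed correlation | At least one p < 0.05 |
|---|---|
| Independent | 43% |
| Within family 0.5, between 0 | 40% |
| Within family 0.8, between 0 | 34% |
| Within family 0.8, between 0.3 | 31% |
| Common 0.5 across all eleven | 30% |
| Common 0.7 across all eleven | 22% |

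These figures cover only the group-by-time tests. The within-group tests and the brain-periphery change correlations are extra.

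**Power per outcome if the primaries are corrected (f(V) = 0.30, N = 90).** Bonferroni at 0.05/11 = 0.00455, by the same noncentral F: 47.7%.

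Benjamini-Hochberg at 5%, simulated with a normal approximation (mean shift √8.1 = 2.85; assumed correlation 0.5 within and 0 between families), average power per truly affected outcome:

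| Outcomes that truly move | Power per such outcome |
|---|---|
| 1 | 51% |
| 3 | 61% |
| 6 | 70% |
| 11 | 78% |

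The two methods use different approximations. On the normal approximation Bonferroni itself gives about 50%, since its critical value of 2.84 almost equals the shift of 2.85. With one true effect the two procedures are therefore nearly the same, and the advantage of Benjamini-Hochberg grows as more outcomes move.

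**The case against.** **The absence of correction is inferred.** The article never says that the primary outcomes go uncorrected. It is a condensed account, and a statistical analysis plan that is not shown may hold a rule. This stands as a limit on wording: a reader might infer that the plan declares uncorrected testing, and it does not. It does not remove the point, because the article does more than stay silent. It states which classes are corrected and by which method. If another document corrects the primaries, this section misdescribes the scheme and still needs rewording.

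**The aim is mechanistic.** The Discussion puts mechanisms ahead of effectiveness, and no rule says that any single significant outcome makes the trial positive. The global-null probability is thus one yardstick among several. That tempers the point. But the outcomes are labelled primary and carry a directional between-group hypothesis. Even if each family is treated as its own claim, three independent tests within a family give 1 − 0.95³ = 14%.

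**The size depends on unknown correlation.** This stands. A reader might take a third as the least possible error rate. It is not: 34% requires zero correlation between families, which sits poorly with the trial's own expectation that central and peripheral changes correlate. Only the 43% follows from the outcome count and alpha alone, and it assumes independence.

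**Correction costs power.** True. But a Bonferroni figure of 48% is close to the worst case for Benjamini-Hochberg and should not be read as its general price.

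**Conclusion.** The point holds. As the article assigns its corrections, the eleven primary group-by-time tests are each made at unadjusted two-sided 0.05, with no ranking, composite or joint-success rule. Under a global null, at least one is significant with probability 43% if the tests are independent, and about 22% to 31% under the stronger correlations assumed above. No value examined comes near 5%.

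The conclusion rests on reading the stated scope of the corrections as complete. The figures below 43% rest on correlations that the documents do not supply. A reader might also infer that the sample size is miscalculated. The documents do not support that on this point: 90 reproduces exactly, but for one outcome at unadjusted 0.05, which the Sample Size section should say.

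**What to change.** In Methods: Statistics and Analysis, extend the plan's own FDR correction to the primary outcomes. Name Benjamini-Hochberg at 5% across the eleven group-by-time tests, list those tests, and fix the rule before any unblinded analysis. This procedure controls the false discovery rate. It limits the family-wise error quantified above only when no outcome truly differs, so the text should claim no more than that.

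In Sample Size, state that 80% power at 90 evaluable participants and f(V) = 0.30 applies to one outcome at unadjusted 0.05, and give the per-outcome power under the correction.

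The change is wording only and needs no new data. The price is lower per-outcome power: about 51% if a single outcome truly moves, rising to 78% if all eleven do, under the assumptions shown in the working. Bonferroni at 0.05/11 would give 48%.

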### Ethical Considerations

The HELI study has been reviewed and approved by the MREC Oost-Nederland on December 2nd 2021 (ToetsingOnline filenumber NL78263.091.21, ClinicalTrials.gov ID NCT05777863). All participants provided written informed consent before study inclusion, and participants were free to opt out of participation at any stage of the study. Obtained study data were only accessible to the research team directly involved in the study, and personal privacy was protected by removing personal identifying information from the dataset. Participants received compensation for travel expenses and trial participation, which were evaluated and approved by the MREC to avoid financial motivation in study participation.

## Results

This work was supported by a Crossover grant (MOCIA 17611) of the Dutch Research Council (NWO), granted in December 2019. Recruitment started in April 2022 and concluded in October 2023. Over this period, a total of 279 people showed interest in participating and enrolled, of which 269 participated in the first round of telephone screening and 235 participated in the second round of telephone screening (see Figure 4). We were able to initially include our goal sample size of 104 participants, but 2 last-minute cancellations resulted in a final included sample size of 102 older Dutch adults. This sample size was subsequently randomized in the two parallel intervention arms, with n=49 participants in the “low-intensity” intervention group and 53 participants in the “high-intensity” intervention group.

